# The HAVEN study—hydroxychloroquine in ANCA vasculitis evaluation—a multicentre, randomised, double-blind, placebo-controlled trial: study protocol and statistical analysis plan

**DOI:** 10.1186/s13063-023-07108-3

**Published:** 2023-04-06

**Keywords:** Hydroxychloroquine, AAV, Auto-immune conditions, ANCA, Vasculitis, Prednisolone

## Abstract

**Background:**

Patients with non-severe ANCA-associated vasculitis (AAV) are often prescribed immunosuppressive medications that are associated with severe side effects and a reduced quality of life. There is an unmet need for safer effective treatments for these patients. Hydroxychloroquine is being explored due to its effect in similar autoimmune conditions such as systemic lupus erythematosus.

**Methods:**

Double-blind, placebo-controlled multicentre trial recruiting 76 patients across 20 sites. Participants will be randomised 1:1 to hydroxychloroquine or placebo in addition to standard of care immunosuppressive therapies over the course of 52 weeks. A phase II selection design will be used to determine hdroxychloroquine’s efficacy, using prednisolone dosage and Birmingham Vasculitis Activity Score as a measure of disease activity. Secondary outcomes will explore other elements of AAV progression, including disease flares and time to remission.

**Discussion:**

This trial aims to explore Hydroxychloroquine as a treatment for patients with AAV. If effective, the need for immunosuppressive treatments such as prednisolone could be reduced. Hydroxychloroquine is safer, cheaper and has fewer adverse effects than conventional immunosuppressive treatments. This could improve patient outcomes while saving money for the NHS.

**Trial registration:**

ISRCTN: ISRCTN79334891. Registered 07 June 2021.

EudraCT: 2018-001268-40. Registered 13 September 2019.

Clinicaltrials.gov: NCT04316494. Registered 20 March 2020.

**Supplementary Information:**

The online version contains supplementary material available at 10.1186/s13063-023-07108-3.

## Background

The systemic vasculitides encompass a group of autoimmune inflammatory diseases affecting blood vessels of all sizes and in any organ or system. They are life-threatening diseases where the body’s defence system becomes overactive, causing inflammation of small blood vessels. The term ANCA-associated vasculitis (AAV) describes a subset of primary small vessel vasculitides characterized by the presence of anti-neutrophil cytoplasmic antibodies (ANCA): granulomatosis with polyangiitis (GPA), microscopic polyangiitis (MPA) and eosinophilic granulomatosis with polyangiitis (EGPA).

AAV are serious multisystem autoimmune disorders that can affect any organ in the body and commonly involve the ear-nose-throat, lungs, kidneys, eyes and joints. Uncontrolled disease activity can lead to organ failure and death. There are approximately 20,000 AAV patients in the UK, with 1300 diagnosed annually [1].

Although immunosuppressive treatments have improved outcomes, mortality is double that of the general population [2], 20% have persistent uncontrolled disease and 50% relapse by 5 years [3], costing > £23 million/year for hospitalisations and reducing patients’ incomes by a quarter [4].

AAV patients have a 20 times higher prothrombotic tendency [5], 3 times higher cardiovascular risk [6] and are at higher risk of immunosuppression related infections and cancer [2]. However, early therapy withdrawal, especially of glucocorticoids, is associated with disease flares, lower quality of life and increased costs [7].

There is an unmet need for safe, effective therapies for non-severe AAV to reduce disease activity, prevent disease progression and damage accumulation and minimise drug toxicity. Safer medications are needed for non-life threatening ANCA vasculitis, where aggressive immune suppressive medications are not appropriate.

Hydroxychloroquine is an effective, safe and inexpensive therapy with an established track record of disease modifying effects in autoimmune rheumatic diseases such as systemic lupus erythematosus (SLE) and Sjögren’s syndrome [8–11]. Hydroxychloroquine is safer than other immunosuppressive treatments (including in pregnancy), and it is steroid sparing, allowing reductions in cumulative prednisolone doses and their adverse effects [9]. Hydroxychloroquine has been used to treat cutaneous vasculitis [12] and rheumatoid vasculitis [10] but has never been assessed in AAV [13]. The pleiotropic effects of hydroxychloroquine on cytokines, neutrophils and autoreactive T and B lymphocytes involved in the pathogenesis of AAV provide a mechanistic rationale for its potential effectiveness [13]. Hydroxychloroquine has beneficial effects on lipids, glucose levels and arterial stiffness [14]. Hydroxychloroquine has antimicrobial [15, 16], antithrombotic [17] and antineoplastic [18, 19] effects that could be useful in immunosuppressed AAV patients. Early treatment with hydroxychloroquine could potentially reduce progression to severe disease and the need for biologic therapy, such as rituximab, which is administered for refractory or relapsing AAV [20–22]. The HAVEN trial aims to investigate this by assessing whether the addition of hydroxychloroquine to background therapy improves clinical response and quality of life in patients with AAV.

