The following exploratory outcomes will be examined:Proportion of patient with incidence of new diabetes mellitus*Proportion of patients with dyslipidaemiaMedian Functional Assessment of Chronic Illness Therapy (FACIT) [25] score at each time point and the median relative change in FACIT score from baseline to week 52/56*Median scores in quality-of-life measures: SF-36 [26], EQ5D [27], Health Assessment Questionnaire (HAQ) [28] and AAV Patient Reported Outcome (PRO) [29] at each time point and the median relative change in the same quality of life measures from baseline to week 52/56*Median Glucocorticoid Toxicity Index (GTI) [30] at each time point and the median relative change in GTI from baseline to week 52/56Median Physician’s Global Assessment (PGA) [31] at each time point and the median relative change in PGA from baseline to week 52/56*Mean ANCA titres at each time point and the median relative change in ANCA titres from baseline to each time point*Proportion of patients with medicine compliance of ≤ 80%Mean absolute values and relative change from baseline to each time point in renal variables: serum creatinine, serum albumin, urine protein to creatinine ratio*

Participants wishing to stop trial medication will be asked to continue trial visits and data collection if willing. Otherwise, they will be withdrawn from the trial.

In the case that a participant withdraws more than 4 weeks since their last hospital visit, they will be invited to attend a withdrawal visit or a telephone interview. Data contributing to the asterisked (*) outcome measures above will be collected if feasible during this visit. Data collected prior to participant withdrawal will be included in the statistical analysis where possible.

It is anticipated that the withdrawal rate for this cohort of patients will be < 5% [21, 32, 33]. No specific plans have been made to ensure participant retention as this low withdrawal rate is based on similar studies in AAV patients. However, participants will be contacted via the telephone between hospital visits which are longer than 4 weeks apart to provide regular contact and encourage participants to report AEs.

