### Sample size calculation

As AAV is uncommon, the required sample size was optimised using a phase II selection theory approach (also known as ‘pick the winner’) as proposed by Simon et al. [34]. The treatment which is ranked as having the lower proportion of patients with uncontrolled AAV (BVAS > 3) (or controlled but with > 7.5 mg prednisolone or other corticosteroid daily) in the final 12 weeks of the study will be selected as the ‘winning treatment’.

A sample size of 72 patients (36 in each arm) will be required to provide 90% probability of correctly ranking hydroxychloroquine as superior to placebo, assuming 50% of patients in the placebo group have uncontrolled AAV (or controlled but with > 7.5 mg prednisolone or other corticosteroid daily) in the final 12 weeks of the study and assuming that the true reduction in this rate due to hydroxychloroquine is 15%. This trial is not designed to demonstrate a statistically significant difference between the two arms, so the type I error rate does not apply.

Seventy-six participants will be recruited to allow for a 5% drop-out rate. This drop-out rate is based on similar trials which had a < 5% drop-out rate [21, 32, 33].

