### Statistical analysis

Due to the use of a selection theory (pick the winner) approach, the main analysis will not include inferential analysis. Instead, the main analysis will involve presenting the descriptive statistics for each treatment arm to demonstrate which treatment is selected (i.e. which treatment group has a lower proportion of participants meeting the primary endpoint criteria). Due to this trial design, no interim analyses have been planned.

The descriptive statistics follow those specified in the outcome measures. The primary outcome and secondary/exploratory outcomes specifying a proportion will be described as the number and proportion of participants meeting that outcome. Secondary/exploratory outcomes specifying median will be described as median and range. Secondary/exploratory outcomes specifying mean will be described as mean and standard deviation.

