#### Subgroup/exploratory analyses

The reporting of descriptive statistics for the primary endpoint and ranking of the two treatment arms will be repeated for the following subgroups:Those deemed compliant with treatment (consumption of > 80% of provided tablets)Those deemed non-compliant with treatment (consumption of ≤ 80% of provided tablets)

These analyses will only be repeated if enough participants meet these criteria for each treatment arm (≥ 5 participants per group).

Additionally, exploratory inferential analyses have been planned. This will involve tests of two proportions for those outcomes specifying a proportion. For the other outcomes, unpaired *t*-tests and Mann Whitney *U* tests will be used dependent on the resultant outcome distribution. For all tests, a one-sided significance level of 10% will be used to determine results of potential interest.

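### Lipids are analysed only as a yes/no proportion and HbA1c values in no listed outcome, although both are measured at screening and weeks 28 and 52; using the values would be more precise at almost no cost

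*Protocol article*

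**What the plan says.** All references are to the protocol article.

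- **Background.** A metabolic benefit is one line of the rationale: "Hydroxychloroquine has beneficial effects on lipids, glucose levels and arterial stiffness". No size is given. The same section ends with the trial's aim, which is clinical response and quality of life.
- **Table 1, Clinical Labs.** Lipids and HbA1c each have three draws: screening, week 28 and week 52. Each therefore has one value before randomisation and two on treatment.
- **Outcome measures, exploratory list.** The one lipid outcome is the proportion of patients with dyslipidaemia. The neighbouring diabetes outcome is "Proportion of patient with incidence of new diabetes mellitus". The list also plans "Mean absolute values and relative change from baseline to each time point in renal variables", and a comparable summary for ANCA titres. Measured lipid and HbA1c values are named in no outcome.
- **Statistical analysis.** The descriptive statistics follow the form given in the outcome list, so an outcome worded as a proportion is summarised as a number and a proportion. For the trial as a whole, "the main analysis will not include inferential analysis".
- **Subgroup/exploratory analyses.** The exploratory inference consists of "tests of two proportions for those outcomes specifying a proportion", with t-tests or Mann-Whitney tests for the rest, and "a one-sided significance level of 10% will be used to determine results of potential interest".

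**The concern.** In this article the wording of an outcome fixes its analysis. Because the lipid outcome is worded as a proportion, three scheduled measurements per participant become one yes/no comparison between arms of about 36, and the screening value has no stated role. Measured HbA1c is collected on the same schedule and has no listed use as a value.

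A threshold count records only whether a participant is above or below the cut-off. Movement on either side of it is lost, and so is the precision gained by comparing each participant with their own starting level. In a trial of this size, even a moderate metabolic effect could easily fail to show. The same list already uses a better form for renal variables, so the lipid outcome is also out of step with its neighbours.

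What is at stake is one exploratory result. The ranking of the two arms on the primary outcome does not depend on it.

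**Working it through.** **1. The plan's own figure.** The Sample size calculation states: "A sample size of 72 patients (36 in each arm) will be required to provide 90% probability of correctly ranking hydroxychloroquine as superior to placebo". The event rates behind this are 50% on placebo and 35% on hydroxychloroquine. With two independent binomials of 36, P(fewer events on hydroxychloroquine) = 0.881 and P(tie) = 0.041. Splitting ties gives 0.881 + 0.041/2 = 0.902, which matches 90%. For drop-out, 72/0.95 = 75.8, rounded up to 76, also as stated. The design figure reproduces. It concerns the primary outcome; nothing in the article sizes the lipid comparison.

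**2. Inputs for lipids.** From the article: 36 per arm, one-sided 10% (z = 1.2816), two-proportion test. Assumed, because the article gives none of them: a normally distributed lipid value; a true shift d of 0.3 or 0.5 SD; placebo prevalence π above the cut-off of 30% or 50%; screening-to-week-52 correlation ρ of 0.5 to 0.8.

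**3. Yes/no at week 52.** The cut-off is c = Φ⁻¹(1 − π), and the treated proportion is p = 1 − Φ(c + d). Power = Φ[(π − p − 1.2816·s0)/s1], where s0 is the pooled and s1 the unpooled standard error. Example with π = 0.50 and d = 0.3: p = 0.382, s0 = 0.1170, s1 = 0.1162. Then (0.1179 − 0.1500)/0.1162 = −0.276, so power is 0.39.

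**4. Week-52 mean adjusted for screening (ANCOVA).** Power = Φ[d/(√(1 − ρ²)·√(2/36)) − 1.2816]. Example with d = 0.3 and ρ = 0.7: 0.3/(0.714 × 0.2357) = 1.782, less 1.2816 is 0.501, so power is 0.69. The relative loss from using yes/no in this example is 1 − 0.391/0.692 = 43%.

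**5. Results.**

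| Shift | Prevalence | Yes/no | ANCOVA at ρ = 0.5 / 0.7 / 0.8 | Power lost |
|---|---|---|---|---|
| 0.3 SD | 30% | 0.36 | 0.57 / 0.69 / 0.80 | 37% / 48% / 55% |
| 0.3 SD | 50% | 0.39 | 0.57 / 0.69 / 0.80 | 32% / 43% / 51% |
| 0.5 SD | 30% | 0.58 | 0.88 / 0.95 / 0.99 | 33% / 39% / 41% |
| 0.5 SD | 50% | 0.65 | 0.88 / 0.95 / 0.99 | 26% / 32% / 34% |

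Simulating the same scenarios gives 0.37 to 0.64 for yes/no and 0.56 to 0.99 for ANCOVA, which agrees to within about 0.02.

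**6. Where the loss comes from.** An unadjusted comparison of week-52 means has power 0.50 at 0.3 SD and 0.80 at 0.5 SD. Dichotomising takes this down to 0.36–0.39 and 0.58–0.65. Adjusting for screening instead takes it up to 0.57–0.80 and 0.88–0.99. Both steps contribute.

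**7. Information kept.** Asymptotic efficiency of yes/no relative to ANCOVA is φ(c)²/[π(1 − π)] × (1 − ρ²). The first factor is 0.576 at 30% and 0.637 at 50%. At ρ = 0.5 the product is 0.43 to 0.48; at ρ = 0.8 it is 0.21 to 0.23. So 52% to 79% of the information is lost.

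**8. Two other ways of counting (simulated, ρ 0.5 to 0.7, prevalence 30 to 50%).**
- *Every case at entry counted as a case throughout:* power 0.19–0.20 at 0.3 SD and 0.25–0.28 at 0.5 SD. Against ANCOVA the loss runs from 1 − 0.204/0.572 = 64% to 1 − 0.248/0.953 = 74%.
- *New cases only, among those free at screening:* power 0.30–0.32 and 0.47–0.50. This is below week-52 prevalence in the same simulations (0.37–0.39 and 0.60–0.64).

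**The case against.** The strongest reply is that this is a selection trial with a descriptive main analysis. The metabolic line is background, the dyslipidaemia outcome is exploratory, and its test only flags results of potential interest. Judging it by power applies a standard that the design sets aside even for its primary outcome. ANCOVA is specified for no outcome in the article, and lipid-lowering treatment started after randomisation could distort a week-52 mean. These points stand as limits on importance. They do not make a threshold count a better use of values already collected, and the loss of precision affects a descriptive comparison too.

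A reader might go further in four ways that the article does not support.

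- **That most of the power is lost.** For a week-52 classification, the loss exceeds one half only at 0.3 SD with correlation 0.8. It is clearly most of the power only if an entry diagnosis always counts as a case, a rule the article does not state.
- **That participants already dyslipidaemic at entry are the cause, and counting new cases the cure.** The wording does differ from "incidence of new diabetes mellitus" for diabetes, but counting new cases only has less power than week-52 prevalence.
- **That the missing definition, time point and handling of entry cases are faults.** The full protocol is held separately and may contain them.
- **That leaving dyslipidaemia out of the minimisation is a defect.** Chance imbalance can affect any characteristic that is not a minimisation factor.

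**Conclusion.** The point holds as a minor one. As the article fixes it, the only lipid analysis is a yes/no proportion, and measured lipid and HbA1c values enter no listed outcome despite three scheduled draws of each. For lipids, dichotomising and ignoring the screening value together cost roughly a quarter to a half of the power (26% to 55% across the grid) and more than half of the information. These sizes depend on the assumed shift, correlation, prevalence and normality; no document figure fixes them. HbA1c was not modelled separately, and the point there is only that its values go unused.

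The metabolic benefit is rationale and not a trial hypothesis. The primary selection and its 90% ranking probability are untouched.

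**What to change.** Add lipid and HbA1c values to the exploratory list, as is already done for renal variables: report each by arm at screening, week 28 and week 52, and give the between-arm week-52 difference adjusted for the screening value (ANCOVA) with its confidence interval. Name the lipid fractions in advance. Keep the dyslipidaemia proportion only as a descriptive supplement, stating its time point and how entry cases count if the full protocol does not already do so. Do not adopt a new-onset proportion as a remedy for power.

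The cost is small: no new visit, sample or participant is needed. There will be a few more exploratory estimates and one method not otherwise used in the article. Lipid-lowering treatment started after randomisation must be noted when the results are interpreted; medications are already recorded at every visit. The change should be made before treatment allocation is unblinded for analysis.

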## Methods

### Trial design

The HAVEN trial is a double-blind, placebo-controlled multi-centre trial following a phase II selection design. Participants will be randomised to receive hydroxychloroquine or placebo in a 1:1 ratio, in addition to standard of care (SoC) maintenance therapy with prednisolone and/or stable doses of azathioprine, methotrexate, mycophenolate, co-trimoxazole or maintenance therapy with B cell depleting therapy (rituximab). Each patient will be treated with adjunctive hydroxychloroquine 400 mg daily or matching placebo for 52 weeks with dose reduction according to actual body weight and renal function. Participants will attend 10 visits across 60 weeks (Fig. 1). At each visit, disease activity will be determined using the Birmingham Vasculitis Activity Score (BVAS), and data will be collected on other measures including further disease activity indicators, treatment adherence, clinical biomarkers and quality of life (Table 1).

**Fig. 1 Fig1:**
[figure not shown]
Flow chart of trial design and participant follow-up

**Table 1 Tab1:** Schedule of enrolment, interventions and assessments from SPIRIT checklist

**Study Visits**^**i**^	**Screen **	**Baseline**	**WK4**	**WK10 Telephone**	**WK16**	**WK 22 Telephone **	**WK28**	**WK 34 Telephone **	**WK40**	**WK44**	**WK48**	**WK52 End of study treatment**	**Follow up WK56**	**Withdrawal**^**ii**^
**Visit Number**	**1**	**2**	**3**	**-**	**4**	**-**	**5**	**-**	**6**	**7**	**8**	**9**	**10**	**-**
**Day (Visit window)**	**Up to 28 days**	**0**	**28** (± 7)	**70** (± 7)	**112** (± 7)	**154** (± 7)	**196** (± 7)	**238** (± 7)	**280** (± 7)	**308** (± 7)	**336** (± 7)	**364** (± 7)	**392** (± 7)	
Patient information and informed consent	X													
**Interventions:**														
IMP dispensing		X	X		X		X		X					
IMP dose recording / review of patient diary			X		X		X		X	X	X	X		X
Prednisolone dose recording	X	X	X		X		X		X	X	X	X	X	X
**Assessments:**														
COVID symptom assessment	X	X	X		X		X		X	X	X	X	X	X
Eye screen												X^iii^		
Eligibility	X	X^iv^												
Randomisation		X												
Medical history, Demographics	X													
Physical exam, Weight, Vital signs^v^, Urine dipstick	X	X	X		X		X		X	X	X	X	X	X
ECG	X				X									
Medications	X	X	X	X	X	X	X	X	X	X	X	X	X	X
BVAS^vi^	X	X	X		X		X		X	X	X	X	X	X
VDI		X			X		X			X		X		
GTI		X					X					X		
Physician’s Global Assessment	X	X	X		X		X		X	X	X	X	X	X
Urine drug screen	X													
SF-36, EQ5D, HAQ, AAV Pro		X		Xvii	X	X^vii^	X	X^vii^		X		X	X	X
FACIT score		X			X		X			X		X	X	X
Adverse event reporting		X	X	X	X	X	X	X	X	X	X	X	X	X
**Clinical Labs:**														
ANCA	X				X		X		X			X	X	X
ESR^viii^, CRP		X			X		X		X			X	X	X
Glucose		X			X		X		X			X	X	X
HbA1C	X						X					X		
Lipids	X						X					X		
Renal profile including creatinine and eGFR^ix^	X	X	X		X		X		X			X	X	X
Full blood count	X	X^x^	X		X		X		X			X	X	X
Liver function tests	X	X^x^	X		X		X		X			X	X	X
Protein: creatinine ratio^xi^	X	X	X		X		X		X	X	X	X	X	X
Viral screen^xii^	X													
Pregnancy test^xiii^	X	X												
**Research Blood Specimens:**														
Hydroxychloroquine levels		X			X		X					X		
Plasma, Serum and Cells^xiv^		X			X		X		X			X		X^xv^

^i^ Patients will be followed up by telephone at weeks 10, 22 and 34 rather than visiting the study centre. The phone call will be structured using the AAV pro questionnaire. See section 6.13 for more details

^ii^ To be arranged if a patient withdraws from the trial but is willing to have a final study visit. This is only necessary in instances where the patient’s last visit was more than 4 weeks ago

^iii^ The eye screen is only required for patients whose eGFR drops below 60ml/min at any point during the trial. The eye screen should take place between week 52 and week 56 visits by a local optometrist

^iv^ The eligibility criteria require BVAS to be scored and for female patients to have a pregnancy test at baseline as well as screening. Other screening procedures do not need to be repeated

^v^ Vital signs to include BP, pulse, respiration rate and temperature

^vi^ BVAS and VDI to be scored locally following training. BVAS scores will be quality checked by a central adjudication panel to ensure consistency

^vii^ Telephone follow up interviews will only use the AAV Pro questionnaire to structure the conversation. The SF-36, EQ5D and HAQ questionnaires will not be included

^viii^ Where ESR is not available, plasma viscosity may be used instead

^ix^ If the patient’s eGFR drops below 60ml/min at any point of the trial they should be invited for an eye screen between week 52 and 56

^x^ If the baseline visit is less than two weeks after screening, these tests do not need to be performed again

^xi^ Protein:creatinine ratio only needs to be performed if urine dipstick for protein shows 1+ or more, but results can be collected if routinely performed when the urine dipstick is negative

^xii^ Patients who test positive for hepatitis B surface antigen, hepatitis B core antibody, hepatitis C antibody or HIV-1 will be excluded

^xiii^ Urine pregnancy test

^xiv^ Plasma and serum collected at all sites. Cells at Guy’s Hospital only

^xv^ Samples only collected if the patient is identified as having a flare

